### Monitoring

2.20

The study will be carried out in accordance with the protocol, as it will be registered. No changes in the study protocol are expected to be made after the study starts. However, in case of any unexpected circumstances requiring alterations of the protocol, changes will be immediately applied to the protocol registry site at https://www.clinicaltrials.gov, and, if relevant enough, reported to the Bioethics committee of each participating institution. An independent Data and Safety Monitoring Board (DSMB) will be created before the start of the study. The DSMB will review data after recruitment from 25%, 50% and 75% of participants to assess the study progress (including rate of recruitment, completeness of data and their appropriate collection) and all the adverse events. The number of recruited patients will be monitored and kept up to date; appropriate changes (i.e., training of the recruiting physicians, study leaflets, addition of new recruitment centres) will be applied to the study procedure and protocol if the pace of recruitment is not high enough (or not sufficient) to finish the study within the established time of 4 years.

## Discussion

3

Currently, there are no standardized protocols for the assessment of tolerance acquisition using the EL approach. Furthermore, scientific evidence supporting the efficacy and safety of the EL in children with HEA remains limited. According to the BSACI guidelines, reintroduction of baked egg as an ingredient may be performed in children aged 12 months or 6 months from the last reaction (15). Additionally, regular ingestion of baked egg may accelerate the acquisition of tolerance to unheated egg and reduce dietary exclusions.

This study will assess the efficacy of the 4-EL compared to the 5-EL in children with confirmed IgE-mediated HEA. Due to limited evidence, high-quality trials are needed. However, no study is perfect, and this trial also has some limitations. The risk of bias is associated with the lack of blinding, which is not feasibility due to the nature of the intervention. Although participant will receive the intervention in both study arms (the 4-EL or 5-EL), some parents may prefer a different ladder than the one assigned (i.e., the shorter arm may be associated with fewer hospital visits). A second limitation is the home preparation of tested foods by caregivers. Although standardized recipes will be provided, a risk of inaccurate food preparation or modification cannot be excluded. To minimize this bias, caregivers will be asked before each challenge, whether any modifications were made, and the total amount and portion of the prepared foods will be weighed. Another limitation is the absence of a formal sample size calculation and the pilot nature of this trial. Due to limited evidence, the sample size was only estimated. However, it is considered sufficient to detect a clinical difference between these two egg ladders and to inform further confirmatory trials.

This rigorously designed RCT will help to compare the efficacy of two ladders: the 4-EL which begins with a higher amount of baked hen's egg proteins (1.5 g), and the 5-EL, in which gradual reintroduction starts with two steps – muffins containing 0.75 g and 1.5 g of egg proteins, respectively. Currently, it is unclear whether the initial reintroduced dose of baked hen's egg protein in children with IgE-mediated HEA, especially those in high-risk groups, should differ from that used in children with mild and moderate non-IgE mediated HEA. This study will be conducted by a research center experienced in RCTs involving children and food allergy. The study team is supported by [name], who serves as a scientific mentor and provides expert oversight in protocol development and clinical decision-making in complex cases. The findings of this RCT will address current evidence gaps and inform guideline development groups regarding the efficacy and safety of the 4-EL in children with IgE-mediated HEA.

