**Methods:**

We will perform an open-label randomized trial with two-parallel arms in two departments if the same academic hospital. A total of 84 children with IgE-mediated HEA will be allocated in 1:1 ratio to introduce hen's egg allergy into their diet according to either 4-EL or 5-EL with 4-week break period between subsequent steps. Oral food challenge (OFC) with tested products at each subsequent step of the EL will be conducted in hospital settings. The primary outcome will be the percentage of children with tolerance to non-heated hen's egg proteins defined as non-allergic reaction to raw hen's egg (0.5–1 egg, depending on the age of the patient) during the last OFC; measured at the end of the 18-week observation period for the 4-EL and 24-week observation period for the 5-EL. Secondary outcomes will include the percentage of children with negative OFC to each EL step; the percentage of children with anaphylaxis (including the percentage of those who were treated with epinephrine); the percentage of children with exacerbation of atopic dermatitis; growth; compliance; and quality of life of the caregivers and parents anxiety about adverse events during their child's OFC.

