Allergology societies in different countries have proposed varying versions of the EL. However, discrepancies exist in both the number of steps included (ranging from 3 to 9 stages) and in the recommended intervals for progressing between each stage (ranging from 1 to 9 months) (12–17). Only one randomized controlled trial (RCT) has assessed the effect of a short-term EL protocol (18 months with 3–6 months break in periods) compared to a long-term protocol (30 months with a 9 months break in period) on hen's egg tolerance acquisition (12). This trial demonstrated a shorter time to achieve tolerance to unheated hen's egg (24 vs. 30 months) and a higher proportion of children attaining tolerance to raw egg (80% vs. 69%) in the short-term arm compared to control group (*n* = 78).

Currently, there are no standardized protocols for the assessment of tolerance acquisition using the EL approach. Furthermore, scientific evidence supporting the efficacy and safety of the EL in children with HEA remains limited.

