### Study objective and hypothesis

2.1

The primary aim of this study is to evaluate and compare the efficacy and safety of a 4-step egg ladder (4-EL) and a 5-step egg ladder (5-EL) in children diagnosed with IgE-mediated hen's egg protein allergy.

We hypothesize that the 4-EL, with 6-week intervals, will be sufficient for assessing tolerance to hen's egg proteins in children with IgE-mediated allergy and will result in a greater proportion of children achieving tolerance to raw egg white, confirmed by OFC, compared to the 5-EL, with the same timeframe. This corresponds to an 18-week tolerance acquisition period in the 4-EL group vs. 24 weeks in the 5-EL group.

There is some evidence suggesting that the introduction of baked egg in high-risk children (e.g., those with a history of anaphylaxis) may be both safe and effective (21). However, it remains unclear whether the initial tested dose of baked hen's egg protein in such cases should be lower than, or the same as, that recommended for the general pediatric HEA population.

Therefore, we decided to compare two ladder protocols: the 4-EL, beginning with a muffin containing 1.5 g of hen's egg proteins, and the 5-EL, in which the first two steps consist of muffins containing 0.75 g and 1.5 g of egg proteins, respectively. This approach allows for a reduced allergen load at initial exposure and a longer cumulative exposure to baked hen's egg proteins. Such a strategy may be more appropriate for specific subgroups of patients, particularly those considered to be at higher risk (21).

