### Study design

2.2

To compare both treatment strategies, we will conduct a multicenter, open-label, randomized superiority trial with two parallel arms and a 1:1 allocation ratio.

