### Sample size justification

2.9

This study is designed as a randomized controlled trial (RCT) to compare the clinical effectiveness and safety of two versions of an egg ladder protocol: one with four steps and the other with five steps, in children with IgE-mediated hen's egg allergy.

A formal sample size calculation based on statistical power was not feasible due to the lack of standardized data regarding allergen content and clinical reactivity across different baked egg preparations used in oral food challenges. As noted in the existing literature, studies assessing the immunological and clinical progression through the egg ladder remain limited, and standardized endpoints have not yet been universally defined.

Therefore, this trial was informed by available clinical evidence and precedent from similar studies involving the milk ladder in cow's milk-allergic children. In particular, a comparable RCT evaluating the impact of introducing baked cow's milk on tolerance development included 84 children (42 per arm) and demonstrated sufficient power to detect clinically meaningful differences (14).

Moreover, a recent randomized trial by De Vlieger et al. (12), which evaluated short- vs. long-term guided gradual egg reintroduction in baked egg–tolerant children, also enrolled 78 children (39 per arm) and successfully identified significant differences in tolerance acquisition timelines.

Based on this evidence and our clinical experience, a total of 94 children (47 per group) will be recruited to allow for an anticipated 10% dropout rate, ensuring that at least 84 participants (42 per group) complete the trial. This sample size is considered both feasible and appropriate to meet the study objectives while allowing an initial exploration of clinical differences between the two egg ladder variants. This pilot trial will generate effect size estimates to inform future confirmatory studies and formal sample size calculations.

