### Statistical analysis

2.19

Descriptive statistics will be used to summarize baseline characteristics. For continuous variables, comparisons between groups will be made using the Student's *t*-test, Mann–Whitney *U*-test or Wilcoxon signed rank test, depending on whether or not the variables are normally distributed. The appropriate statistical test will be employed to compare percentages, either the χ^2^ test or Fisher's exact test.

For continuous outcomes, the differences in means or medians (depending on the distribution of data), and for dichotomous outcomes, the relative risk (RR) and number needed to treat (NNT), all accompanied by a 95% CI, will be calculated. The difference between study groups will be considered statistically significant if the *p*-value is less than 0.05, if the 95% CI for RR does not include 1.0, or if the 95% CI for mean difference does not include 0. All statistical tests will be two-tailed and performed at the 5% level of significance.

An intention-to-treat (ITT) analysis including all randomised participants, regardless of protocol adherence or withdrawal, will be applied. A per-protocol analysis that includes all participants who finish the study according to the protocol will also be performed.

The number of missing data with reasons will be reported for each study arm, and compared qualitatively between groups, if feasible. Multiple imputation methods for missing data will be applied to address missing data, as recommended (34).

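### The Discussion calls the sample size sufficient to detect a clinical difference, but no effect size or power supports this, and the numbers allocated and completing are not stated consistently

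*Protocol article*

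**What the plan says.** Section 3 (Discussion) lists the missing sample size calculation and the pilot nature of the trial as limitations. It then says of the size that "it is considered sufficient to detect a clinical difference between these two egg ladders".

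Section 2.9 states: "A formal sample size calculation based on statistical power was not feasible". It takes 84 (42 per arm) from a randomised trial of baked cow's milk and mentions a 78-child egg trial as a further precedent. It recruits 94 (47 per arm) to allow for 10% dropout, "ensuring that at least 84 participants (42 per group) complete the trial". It describes the study as an initial exploration and a pilot that will supply effect estimates for later trials.

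The abstract gives another number: "A total of 84 children with IgE-mediated HEA will be allocated in 1:1 ratio".

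Section 2.2 describes an "open-label, randomized superiority trial with two parallel arms and a 1:1 allocation ratio", and section 2.19 adds: "All statistical tests will be two-tailed and performed at the 5% level of significance". The primary outcome (section 2.11.1) is binary: a negative OFC at the last ladder step. Under section 2.5.3, a child with a positive OFC at any step takes no further part. Section 2.19 specifies an intention-to-treat analysis of all randomised children.

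**The concern.** Calling a size sufficient to detect a difference is a claim about power. It needs an effect size, and the document names none. Section 2.9 says the calculation could not be done, so the claim in section 3 has no source. The baked-milk precedent is described as adequately powered, but its effect size is not given, so it cannot be carried over to two egg ladders.

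The abstract and section 3 say the findings will inform guideline groups. If the true difference is moderate, a non-significant result is the likely outcome. A reader told that the trial could detect a clinical difference may take that result as evidence that there is none.

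The counts add a second problem. A reader cannot tell whether 84 or 94 children are randomised, or whether the 84 who complete are children who reach the final OFC or children with a known primary outcome.

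**Working it through.** **Inputs.** Two-sided 5% test (section 2.19); 1:1 allocation (section 2.2); 94 recruited, 10% dropout, 84 completing (section 2.9); 80% vs 69% tolerant in the short- vs long-term egg reintroduction trial, and 69% pooled egg-ladder tolerance (95% CI 50% to 85%) with baked-egg tolerance of 70% to 97% (section 1). The 80% vs 69% pair is an assumption here, not the plan's planning effect.

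**The plan's own arithmetic.** 84/0.9 = 93.3, rounded up to 94; 42/0.9 = 46.7, rounded up to 47. Conversely, 94 × 0.9 = 84.6. The dropout inflation reproduces. The 84 itself cannot be derived from any stated power or effect.

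**Power for 80% vs 69%.** Pooled normal formula: power = Φ{[d − 1.96·√(2p̄(1−p̄)/n)] / √[(p₁(1−p₁) + p₂(1−p₂))/n]}, with d = 0.11 and p̄ = 0.745.

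At n = 42: (0.11 − 1.96 × 0.0951)/0.0944 = −0.81, so power = 0.209.

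| Per arm | Normal formula | Exact, chi-square | Exact, Fisher |
|---|---|---|---|
| 42 | 20.9% | 21.4% | 15.4% |
| 47 | 22.9% | 23.0% | 16.7% |

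For 80% power at these rates, n = [1.96·√(2 × 0.745 × 0.255) + 0.842·√(0.16 + 0.2139)]²/0.11² ≈ 246 per arm.

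**Difference detectable with 80% power at 42 per arm.** From a 69% base: 23.1 points (exact chi-square), 23.8 (normal formula), 24.6 (Fisher), so about 23 to 25 points. From a 50% base the normal formula gives about 29 points.

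**Expected precision at 42 per arm.** Half-width of the 95% CI for the risk difference = 1.96·√(2p(1−p)/42):
- p = 0.50: 21.4 points
- p = 0.69: 19.8 points (18.5 for 80% vs 69%)
- p = 0.85: 15.3 points

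That is about 15 to 21 points over the cited range, and about 19 near 69%.

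**Completers.** After 10% dropout, 84.6 children remain before any exclusion for a positive OFC. If completing means reaching the final OFC, the cited baked-egg range applied at the first step alone leaves 84.6 × 0.70 = 59 to 84.6 × 0.97 = 82. Both are below 84, before any loss at the middle steps. The document gives no pass rates by step, so the actual number cannot be derived.

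**The case against.** The strongest reply is that the plan never adopts 80% vs 69%. Those rates compare short- with long-term reintroduction over many months, in children who already tolerated baked egg. Section 3 does not say that 11 points is the clinical difference, and a gap of about 24 points from 69% would be detected with 80% power. This stands: 21% is conditional, and a reader should not infer that the plan's own design figures give it. It does not rescue the claim, because no other effect size is offered in its place.

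A second reply is that a child stopped by an early positive OFC has not acquired tolerance and can be counted as not tolerant under intention to treat. The primary analysis set need not shrink, and completing is undefined. This also stands. A reader might want to put a number on those reaching the final OFC, but that requires assumed pass rates. At 69% overall tolerance after 10% dropout, it is about 58 if every failure falls at the first step (84.6 × 0.69) and about 85 if every failure falls at the last.

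Two further inferences are tempting and unsupported:
- That the egg precedent contradicts the plan. Section 2.9 cites that trial for how long tolerance took to develop, so the size of its difference in proportions contradicts nothing.
- That section 2.1 makes a not-worse claim in saying the 4-step ladder "will be sufficient for assessing tolerance to hen's egg proteins in children with IgE-mediated allergy". The same sentence goes on to predict a greater proportion tolerant than with the 5-step ladder, which is a superiority hypothesis and agrees with section 2.2.

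Finally, no passage says that a non-significant result will be read as equivalence, and section 3 does list the missing calculation as a limitation. The misreading is a risk that the wording creates, not a stated plan.

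**Conclusion.** The point holds in limited form. The sufficiency statement in section 3 is unsupported and sits against section 2.9. Conditional on 80% vs 69%, power is about 21% (chi-square) or 15% (Fisher) at 42 per arm, and about 23% or 17% if all 94 are analysed. From a 69% base, only differences of about 23 to 25 points are detectable with 80% power.

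The 84 allocated in the abstract contradicts the 94 recruited in section 2.9. The assurance of 84 completers makes no visible allowance for exclusions after a positive OFC. It fails if completing means reaching the last OFC, and can stand if it means having a known primary outcome. The size of the shortfall under the first meaning cannot be calculated from the document.

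**What to change.** Text changes only:

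1. Section 3: delete the statement that the size is sufficient to detect a clinical difference. State instead that, with 42 per arm and a 69% base, only differences of about 23 to 25 points are detectable with 80% power.
2. Section 2.9: give the expected 95% CI half-width for the risk difference, about 15 to 21 points across the cited 50% to 85% tolerance range and about 19 near 69%.
3. State that a non-significant result will not be read as equivalence of the two ladders.
4. Give 94 randomised throughout, including the abstract.
5. Section 2.9: replace the assurance of 84 completers with 84 children having a known primary outcome after 10% dropout, counting those stopped by an earlier positive OFC as not tolerant.

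The cost is that the stated figures look less favourable. No patients, visits or procedures are added.
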